**Figure 1 F1:**
[figure not shown]
**Time schedule of enrolment, interventions, and assessments for participants.** Routine tests (APTT, platelets, D-dimer, AT, leukocytes, CRP, PCT, hematocrit), anti-Xa, and urine and plasma NGAL and Cr are measured at baseline. Following randomization, the patient will receive sc enoxaparin according to group allocation. Bedside clinical assessment for VTE and bleeding using validated scoring systems (Well's scores, HEME tool) will be conducted, and samples for hematocrit and platelet count will be taken daily. Bilateral lower extremity CUS will be conducted on the 1st, 3rd and 7th day of inclusion. Once weekly CUS (more frequent if DVT is suspected), as well as samples for peak anti-X_a_ (measured at 4 hours after enoxaparin dose) and trough anti-X_a_ (measured at 20 hours after enoxaparin dose) will be taken. Spiral pulmonary CT angiography and echocardiography will be performed on clinical suspicion of PE. During CRRT-free intervals with CrCl <30 ml/min/1.73 m^2^, group allocation will be discontinued and participants will receive 40 mg enoxaparin QD until the CrCl is >30 ml/min/1.73 m^2^ when enoxaparin dose according to group allocation will be resumed. Samples of urine and plasma will be taken for NGAL and Cr during CRRT-free intervals. APTT, Activated partial thromboplastin time; anti-Xa, Antifactor Xa; AT, Antithrombin; CRP, C-reactive protein; PCT, Procalcitonin; NGAL, Neutrophil gelatinase-associated lipocalin; Cr, Creatinine; sc, subcutaneous; VTE, Venous thromboembolism; CUS, Compression ultrasound; DVT, Deep venous thrombosis; CT, Computed tomography; PE, Pulmonary emboli; CRRT, Continuous renal replacement therapy; CrCl, Creatinine Clearance; QD, Once daily; HIT, Heparin-induced thrombocytopenia; ICU, Intensive care unit.

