### Interventions

The intervention for the treatment arm will be 1 mg/kg enoxaparin sc QD, and the intervention for the control arm will be 40 mg enoxaparin sc QD. Enoxaparin will be administered to the thigh or abdomen of the study patients.

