### Modifications

Project medicine will be adjusted in several situations. If creatinine-clearance (CrCl) is <30 ml/min/1.73 m^2^ during CRRT-free intervals, group allocation will be discontinued and participants will receive 40 mg QD. Once CrCl is >30 ml/min/1.73 m^2^, group allocation will be resumed. In the event of VTE, group allocation will be discontinued, and patients will receive a full treatment dose of enoxaparin. Enoxaparin will be temporarily discontinued in the case of oozing, and packed red blood cells, fresh frozen plasma, and protamine sulphate may be administered at the discretion of the attending physician. Enoxaparin will be resumed according to the group allocation when oozing is no longer observed. Should the platelet count decrease to less than 50 × 109/L, or if there is an unexplained platelet count decrease to less than 50% of baseline, or other suspicion of HIT, enoxaparin will be stopped and mechanical prophylaxis or the HIT-safe anticoagulant, argatroban(Novastan™; Swedish Orphan Biovitrum A/S, Lyngby, Denmark), will be started. The patient will be evaluated by the 4 T’s clinical scoring system [18] and blood samples will be taken for PF4/heparin enzyme-linked immunosorbent assay (ELISA) and 14C-platelet serotonin release assay.

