### Examination and blood tests

Anti-Xa, activated partial thromboplastin time (APTT), platelets, D-dimer, antithrombin (AT), leukocytes, c-reactive protein (CRP), procalcitonin (PCT), hematocrit, urine and plasma NGAL, urine and plasma creatinine (Cr) are all measured at baseline. Peak and trough anti-X_a_ will be measured on day three, and once weekly. We will record the urine output prior to discontinuation of dialysis, and measure NGAL and Cr during CRRT-free intervals. All patients will have daily hematocrit and platelet count measured during the study period. Other parameters will be measured as per the departments’ norm. Samples for anti-Xa activity will be analyzed in a blinded fashion using a validated chromogenic assay kit (COAMATIC Heparin, Chromogenix, Instrumentation Laboratory Company, Lexington, Kentucky, United States). NGAL in urine and plasma will be quantified by particle-enhanced turbidimetric immunoassay (NGAL Test™, Roche Modular P apparatus, BioPorto Diagnostics A/S, Gentofte, Denmark) according to the manufacturer’s instructions.

Patients will undergo daily bedside clinical assessment for bleeding or VTE using validated tools for the ICU population [11,19,20]. Bilateral lower extremity CUS at 1-cm intervals from the iliac/common femoral vein to the popliteal vein will be conducted on the first, third, and seventh day of inclusion. CUS will then be repeated on a weekly basis (more frequently if DVT is clinically suspected). All positive CUS will be verified by a radiologist. Serial ultrasound examinations will be terminated if a positive study for DVT is obtained. Spiral pulmonary CT angiography and echocardiography will be performed on clinical suspicion of PE.

Patients will be followed until one of the following occurs: a combination of VTE and renal recovery, a combination of HIT and renal recovery, ICU death or discharge, or a change from continuous to intermittent dialysis.

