	[name]	Reviewing progress of study
	[name] [name]	Approving changes to the protocol
	[name]	Budget administration
	[name], DMSc	Advice for lead investigators
Trial management committee	[name], MB ,BS; EDIC	Decide when site visit will occur
	[name], PhD	Data verification
	[name] [name]	Randomization
	[name]	Provide annual risk report to Danish Health and Medicines
	[name] [name]	Authority and Danish national scientific ethical committee
	[name]	Serious unexpected suspected adverse events (SUSAR) reporting
	[name], DMSc	
Data manager	[name]	Maintenance of trial IT system and data verification
Data monitoring committee	[name] [name]	Review the interim analysis.
	[name] [name], PhD	Communicate the outcome of its deliberations to the Trial Steering Committee.
	[name] MD, EDIC	Independent from the sponsor and the other committees.
	[name] [name]	

We will analyze data from all randomized patients according to their assigned group (intention-to-treat principle). We will use either estimating-equation methods or continuous repeated measures (a statistical model) in the event of missing data. All baseline demographic values for these two groups will be compared, using the Student’s *t*-test or Mann-Whitney rank sum test for continuous variables and chi-squared (χ^2^) or Fisher's exact test for categorical variables.

The primary outcome VTE will be compared between the two groups. Four pre-specified subgroup analyses based on: 1) the patient's ICU admission (surgical versus medical), 2) center experience, 3) presence or absence of edema, and 4) presence or absence of vasopressor or inotropes use will be performed.

Multiple regression analysis will conducted to evaluate: 1) the influence of vasopressor, respiratory support, comorbidity, organ dysfunction scores, and CrCl on the incidence of VTE and bleeding between groups; and 2) to examine the relationship between biomarker, demographic variables, comorbidity, and Acute Kidney Injury Network classification.

The prediction ability of urine output and NGAL for successful discontinuation of CRRT will be assessed with the area under the receiver operating characteristic (ROC) curve method. Anti-Xa levels will be analyzed by repeated analysis modelling. For survival analysis, we will calculate hazard ratios and associated 95% confidence intervals using Cox regression analysis and the Kaplan-Meier method with log-rank testing.

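### Anti-Xa is sampled whatever enoxaparin dose is in use and analysed only by assigned group, so under the planning assumptions it understates the contrast between levels on 1 mg/kg and on 40 mg

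*Protocol article*

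**What the plan says.** The section on interventions fixes the allocated doses as 1 mg/kg daily against 40 mg daily, both subcutaneous.

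Sampling follows the calendar. Under Examination and blood tests, "Peak and trough anti-X_a_ will be measured on day three, and once weekly". The Figure 1 legend adds the clock times: "samples for peak anti-X_a_ (measured at 4 hours after enoxaparin dose) and trough anti-X_a_ (measured at 20 hours after enoxaparin dose) will be taken". Neither place requires the dose before the sample to be the allocated one. The same section ends serial leg ultrasound after a positive DVT, but states no such end for anti-Xa sampling.

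Modifications takes patients off the allocated dose in defined situations. In CRRT-free intervals with creatinine clearance below 30 ml/min/1.73 m², "group allocation will be discontinued and participants will receive 40 mg QD". After a thrombosis, "In the event of VTE, group allocation will be discontinued, and patients will receive a full treatment dose of enoxaparin". Two further rules interrupt or stop the drug: "Enoxaparin will be temporarily discontinued in the case of oozing", and it is stopped for low platelets or suspected HIT.

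These changes do not by themselves end follow-up. VTE or HIT ends it only together with renal recovery. Otherwise it runs to ICU death or discharge, or to a change to intermittent dialysis.

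On analysis, Sample size and statistical methods gives a general rule, "We will analyze data from all randomized patients according to their assigned group (intention-to-treat principle", and one sentence on this outcome: "Anti-Xa levels will be analyzed by repeated analysis modelling".

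**The concern.** Anti-Xa activity measures drug exposure. A sample taken while a treatment-arm patient is on 40 mg, or while a patient in either arm is on a full treatment dose, says nothing direct about the level reached on the allocated dose. Averaged by arm, such samples mix dose states.

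This affects what the trial can say about levels. The Background rests the choice of dose on an earlier study in which weight-based dosing, unlike 40 mg, gave satisfactory anti-Xa levels. The Discussion aims to confirm 1 mg/kg as the optimal dose. Readers will take the anti-Xa result as the level on 1 mg/kg against the level on 40 mg. A by-arm mean alone does not answer that question, and the mixing tends to narrow the gap. The primary VTE analysis is not affected.

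**Working it through.** **Planning figures.** The document gives no figure for anti-Xa. The VTE rates used below are those of the sample-size paragraph: 40% in control and a 40% relative reduction, so 0.40 × 0.60 = 24% on 1 mg/kg. These reproduce the stated size. With mean proportion 0.32, n = [1.96·√(2·0.32·0.68) + 0.8416·√(0.40·0.60 + 0.24·0.76)]² / 0.16² = (1.293 + 0.547)² / 0.0256 ≈ 132.3, that is 133 per group (power 80.2%).

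**Assumptions not in the document.** Weight is 80 kg (eligible range 45 to 150 kg), and anti-Xa is proportional to dose. The share of samples on substituted 40 mg, the share of a VTE patient's samples that fall after the VTE, and the full treatment dose are each given a range.

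**Step 1: substituted 40 mg only.** Let f be the share of treatment-arm samples taken on 40 mg. The treatment-arm mean dose is 80(1 − f) + 40f. The control mean stays at 40 mg whatever its own share, because the substitute equals its allocated dose.

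| f | Treatment mean (mg) | Control mean (mg) | Ratio | Difference (mg) |
|---|---|---|---|---|
| 0 | 80 | 40 | 2.0 | 40 |
| 20% | 72 | 40 | 1.8 | 32 |
| 40% | 64 | 40 | 1.6 | 24 |

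The difference shrinks by the factor (1 − f). The direction is the same at every eligible weight, since 1 mg/kg is at least 45 mg.

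**Step 2: full treatment dose after VTE only.** At the planning rates 133 × 0.40 ≈ 53 control and 133 × 0.24 ≈ 32 treatment patients have a VTE. These are ceilings on the number who can contribute full-dose samples, since each must still be in follow-up at a later draw. Let s be the share of such patients' samples that fall after the VTE and F the full daily dose. The shares of all samples on F are then 0.24s (treatment) and 0.40s (control).

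- s = 25%, F = 80 mg: treatment 0.94·80 + 0.06·80 = 80.0; control 0.90·40 + 0.10·80 = 44.0; difference 36.0 mg.
- s = 50%, F = 160 mg: treatment 0.88·80 + 0.12·160 = 89.6; control 0.80·40 + 0.20·160 = 64.0; difference 25.6 mg.

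**Step 3: both, with f = 20%.**

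- s = 25%, F = 80 mg: treatment 0.74·80 + 0.06·80 + 0.20·40 = 72.0; control 44.0; difference 28.0 mg (70% of 40 mg).
- s = 50%, F = 160 mg: treatment 0.68·80 + 0.12·160 + 0.20·40 = 81.6; control 64.0; difference 17.6 mg (44% of 40 mg).

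**Step 4: when the direction would reverse.** Write gT and gC for the shares of treatment and control samples on F. Full-dose samples change the difference by gT(F − 80) − gC(F − 40). At F = 160 mg this is negative unless gT exceeds 1.5·gC (120/80). At F = 80 mg it is never positive. The planning rates put gT at 0.6 of gC when s is the same in both arms.

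**The case against.** The strongest reply is that the by-arm analysis is not wrong. It estimates the effect of the assigned strategy, including the dose changes that the protocol prescribes, and it keeps the randomized comparison. That stands. A reader might infer that the by-arm analysis is biased and should be replaced. The documents do not support this, and a restricted analysis has its own weakness: VTE, bleeding and suspected HIT arise after randomization and may depend on dose, so the remaining samples come from selected patients.

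A second reply is that one sentence on modelling leaves room for an analysis plan, not shown here, to add a dose term or an on-dose analysis. That is fair. However, what this document does fix, for all data and with no exception for an exposure measure, is analysis by assigned group.

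Three further readings are tempting but not supported.

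- *Levels in the 1 mg/kg arm are biased down.* Full-dose samples raise that arm too. In the second scenario of step 3 its mean is 81.6 mg, slightly above 80. It is the contrast that shrinks.
- *Held doses pull down the arm that bleeds more.* Samples are timed from an enoxaparin dose, so with the drug stopped they would probably be missing, not low. The trial also hypothesizes no increase in bleeding.
- *Accumulation on 1 mg/kg is hidden and a better analysis would reveal it.* In CRRT-free intervals with low clearance the dosing rule puts patients on 40 mg, so no analysis of these samples can show levels on 1 mg/kg in that state.

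It also stands that the off-allocation share is unknown, that a change to intermittent dialysis ends follow-up and so limits CRRT-free time, and that anti-Xa is one of several secondary outcomes.

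**Conclusion.** The point holds as a limit on interpretation. Analysed only by assigned group, anti-Xa describes the assigned strategy and not levels on the two doses. Under the planned VTE rates and the protocol's own dosing rules, it understates the contrast between those levels.

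The size cannot be derived from the document. For an 80 kg patient, with level proportional to dose, the dose ratio falls from 2.0 to 1.8 or 1.6 if 20% or 40% of treatment-arm samples are taken on 40 mg. With full-dose samples after VTE as well, and 20% of samples on 40 mg, 44% to 70% of the 40 mg contrast remains over the ranges assumed. The direction rests on VTE not being clearly more frequent on 1 mg/kg than on 40 mg. The change is worth making because it is cheap and because dose state may be hard to reconstruct later.

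**What to change.** Keep the by-arm repeated-measures analysis. Prespecify beside it a comparison restricted to samples drawn after a dose given under group allocation. Leave out samples from CRRT-free intervals with creatinine clearance below 30 in **both** arms, although the control dose is unchanged there, so that the same clinical state is removed from each. Leave out full-dose samples after VTE. Label the result as exposure while on the allocated dose, not as a randomized effect.

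If the case report form does not already do so, record with each sample the dose state (allocated, substituted, full, held) and CRRT status. Recording the state and not the milligrams protects the blind, since only the administering nurses know the dose; actual doses can be linked after database lock. Tabulate excluded samples by arm and reason.

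The cost is a short addition to the analysis section and, at most, two entries on the sample form. No extra blood is drawn and no dosing rule changes. The restricted analysis has fewer samples and is open to post-randomization selection, which is why the by-arm analysis stays.

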## Discussion

LMWHs at standard doses appear to protect ward patients against VTE, but what is less clear is the optimal dose suitable for ICU patients. ICU patients with AKI present a particular challenge because of their increased risk of bleeding and thrombosis. Existing guidelines in Denmark recommend 40 mg enoxaparin for thromboprophylaxis, but this is thought to be inadequate. A previous pharmacokinetic trial suggested that a dose of 1 mg/kg enoxaparin may offer optimal thromboprophylaxis [17]. Our current study aims to confirm 1 mg/kg enoxaparin is the optimal dose in this high-risk population. As the study design is one of a randomized double-blinded multicenter trial, it should be considered a high quality trial aiming to provide class I evidence of the primary endpoint.

So far, only one type of LMWH (dalteparin) has won approval for use in patients with severe renal insufficiency [22]. Critically ill patients have decreased levels of protein, and thus a larger free fraction of enoxaparin. The volume of distribution of enoxaparin is only 5 L and this, coupled with a small molecular weight, allow for normal dosing as the drug would be expected to be cleared by the high volumes of fluid employed in hemofiltration. Thus, our study has implications for clinical practice as our findings may challenge the premise that selected LMWHs should be avoided in such patients.

Finally, there are currently no established guidelines for the discontinuation of dialysis. We seek to use a combination of a clinical indicator (urine volume) and a biomarker (NGAL) to predict renal recovery.

## Trial status

This trial is active. Enrolment began in March 2013 and will continue for two years.

## Abbreviations

APTT: Activated partial thromboplastin time; AKI: Acute kidney injury; anti-Xa: Antifactor Xa; AT: Antithrombin; CRP: C-reactive protein; χ^2^: Chi-squared; CUS: Compression ultrasound; CT: Computed tomography; CRRT: Continuous renal replacement therapy; CVVHD: Continuous veno-venous hemodialysis; CVVH: Continuous veno-venous hemofiltration; Cr: Creatinine; CrCl: Creatinine Clearance; DMC: Data Monitoring Committee; DVT: Deep venous thrombosis; ELISA: Enzyme-linked immunosorbent assay; FATE: Focused Assessed Transthoracic Echocardiography; FBI: Feasible strategy for preventing blood clots in critically ill patients with acute kidney injury; GCP: Good Clinical Practice; HIT: Heparin-induced thrombocytopenia; ICU: Intensive care unit; INR: International normalized ratio; LMWH: Low- molecular-weight heparin; NGAL: Neutrophil gelatinase-associated lipocalin; OUH: Odense University Hospital; QD: Once daily; PCT: Procalcitonin; PE: Pulmonary emboli; ROC: Receiver-operator characteristic; sc: Subcutaneous; UFH: Unfractionated heparin; VTE: Venous thromboembolism.
